### Study medication

The investigational drugs used in the study are a test drug and a control drug. The two drugs are impossible to differentiate from each other based on their external appearances.

The open-label study drug (IDEC-C2B8) after the initial phase is identical to the study drug used in the blinded phase excluding the packaging and labeling.

Zenyaku Kogyo Co., Ltd. has provided the study drugs of both test drug and placebo, and subsequently distributed to institutes that have enrolled patients in this trial.

#### Overview of the test drug

Development code name and International non-proprietary namesDevelopment code name: IDEC-C2B8.International non-proprietary names: rituximab.[Japanese accepted names] (English name) rituximab (genetic recombination)Description: Chimeric anti-CD20 monoclonal antibody with mouse anti-CD20 antibody variable regions and human constant regions (IgG1κ) (molecular weight: 144,510 Da)Special notes: IDEC-C2B8 has been approved for the treatment of CD20-positive B-cell lymphoproliferative disease, CD20-positive B cell non-Hodgkin’s lymphoma, ANCA-related vasculitis, chronic idiopathic thrombocytopenic purpura, Wegener’s granulomatosis, systemic lupus erythematodes, and complicated steroid dependent / frequently relapsing nephrotic syndrome in Japan and it is already on the market. The commercial products are designated as biological products.

### Prohibited combination therapy or concomitant medication

Combination therapy using following drugs is prohibited during the period of clinical trial (the consent date up to the end of the observation period).Commercial rituximab.Immunosuppressants or alkylating agents having an immunosuppressive effect, unless cases determined to be treatment failure.Plasma exchange.Live vaccines.Other investigational drugs or unapproved drugs in Japan.

### Screening

When investigators observe a recurrence of NS in study candidate patients, they describe this clinical trial to the relevant subjects and obtain their written consent to participate in the trial. After consent is obtained, screening tests are performed to verify eligibility as a subject. If the eligibility of patients for this trial is confirmed after the screening period, the patients will be assigned within 7 days of confirmation of remission after relapse.

### Randomization

Patients will be randomly assigned to the IDEC-C2B8 or placebo group at a 1:1 ratio. Randomization will be performed using the stratification permuted block method. The assignment adjustment factors are frequent recurrence/steroid dependency. All participating physicians and other investigators will remain blinded to the trial results until follow-ups are completed.

### Binding

JSKDC10 is a placebo-controlled double-blind clinical trial. Registration and assignment are done using the data center assignment program. Only drug numbers assigned to the patient will be displayed to the data center personnel.

The allocation code for the allocation program is entered by the registration and allocation personnel. However, blinding is protected as the assignment code corresponding to the drug number and will not be accessed except at the entry point.

### Procedures

The investigators have to do the first administration of the investigational drug within 14 days after assignment (the first administration date of the investigational drug is set to be Blinded Day 1, week 1). The investigational drug or placebo will be administered using two 375 mg/m^2^ doses (maximum dose: 500 mg) at weekly intervals (Blinded Day 1 and 8). Premedication consisting of acetaminophen, d-chlorpheniramine maleate and methylprednisolone are to be given 30 min prior to the investigational drug infusions to decrease the incidence and severity of infusion reactions. Prednisolone treatment for relapse during the observation period will follow the ISKDC regimen.

### Blood sampling (Tables 1 and 2)

During the clinical trial period, investigators will perform observation, examination, and survey according to a predetermined schedule in this protocol. On all days of investigational drug administration, blood samples are taken immediately prior to administration.

**Table 1 Tab1:**
[figure not shown]
Schedule (Blinded period)

**Table 2 Tab2:**
[figure not shown]
Schedule (Unblinded period)

### Conditions for urgent allocation code disclosure

The investigator may request disclosure of the subject’s emergency allocation code if any of the following situations apply:The subject experiences a severe adverse event that leads to death or life-threatening.The subject experiences a serious adverse event, and the information is judged to be essential for deciding on the treatment of other subjects.Treatment failure occurs.

### Outcomes

The primary endpoint is the time of relapse-free survival during the blinded observation period (days 1–365), assessed as the period from the date of assignment/allocation until that of the first relapse following the commencement of investigational drug administration. Secondary endpoints are the time to treatment failure, total steroid dosage, and changes in the number of B-cells in peripheral blood. Other endpoints are the time of relapse-free survival during the unblinded observation period (days 1–365), IDEC-C2B8 blood concentration, HACA production ratio, and adverse events. Adverse events will be recorded throughout the trial period and assessed using the Japan Clinical Oncology Group (JCOG) Japanese-language version (September 12, 2017) of the Common Terminology Criteria for Adverse Events version 4.0.

### Sample size

A Kaplan–Meier plot of the open-label randomized controlled trial reported from the previous study [6] revealed relapse-free rates at 1 year of 0.66 in the rituximab group and 0 in the steroid alone group. Based on these results, assuming an exponential distribution for relapse-free survival and assuming that the relapse-free rate in 1 year of steroid treatment alone was 0.01 as the placebo group, the hazard rates were 0.42 for the rituximab group and 4.60 for the steroid monotherapy group, resulting in a hazard ratio of 0.09. If the registration period is 17 months, and the observation period of the blinded phase is 12 months, resulting in a total clinical trial period of 29 months, to test the superiority using a significance level of 5% (two-sided) and a detection power of 80%, the required number of the patients was estimated to be 10 per group. At 1-year relapse-free rates of 0.50, 0.40, and 0.30 in the rituximab group, the required numbers of the patients calculated under similar conditions were 12, 13, and 16 per group, respectively. Considering the possibility of withdrawal of consent after participation in the study or the loss of subjects to follow-up and uncertainty for the estimation of 1-year relapse-free rates in placebo group, we set the target sample number to 40 patients (20 in each group).

### Statistical analysis

The objective of the primary analysis (the primary endpoint) in this clinical trial is to examine whether the IDEC-C2B8 group has significantly longer relapse-free survivals than the placebo group. The “relapse-free survival between the two groups will be equal” null hypothesis will be tested using the stratified log-rank test with the subject population receiving at least one dose of the investigational drug administration and measured the data for the assessment of primary endpoint (full analysis set). If the relapse-free survival is shorter in the IDEC-C2B8 group than in the placebo group, the test is one-sided because statistical significance is not important. One-sided significance level was set at 2.5%. If recurrence free survival is significantly longer in the IDEC-C2B8 group than in the placebo group, it can be concluded that IDEC-C2B8 is a useful treatment. Cumulative relapse curves and estimation of time to relapse will be performed using the Kaplan-Meier method and stratified log rank test of time to treatment failure.

The following analyses for the secondary and other endpoints are planned.

The total steroid dose in the blinded observation period will be analyzed using the analysis of covariance.

Median of the time to normalization of peripheral blood B-cells and its 95% confidence interval will be estimated using the Kaplan-Meier method.

The relationships of normalization of the number of peripheral blood B-cells with the presence or absence of relapse and with adverse events will be evaluated in each blinded observation period using Fisher’s exact test.

The proportion for the HACA production in each period with its 95% confidence interval will be estimated and the relationship of the presence or absence of HACA with adverse events will be evaluated in each period by Fisher’s exact test. IDEC-C2B8 blood concentration will be summarized to maximum blood concentration (C_max_), half-life period (T_1/2_), mean residence time (MRT) and area under the concentration-time curve (AUC), and the mean and standard deviation of these parameters will be calculated.

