### Study patients

The inclusion criteria for patients are as follows:Fulfill the diagnostic criteria of idiopathic NS (the International Study of Kidney Disease in Children [ISKDC] idiopathic NS diagnostic criteria are used as a reference during the patient’s initial diagnosis).Younger than 18 years at the time of onset of idiopathic NS.Diagnosis of frequent relapse (two or more relapses within 6 months after initial remission or four or more relapses within any 12-month period) or steroid dependence (two consecutive relapses during steroid therapy dose reduction or within 2 weeks of discontinuation of steroid therapy), as well as confirmation of those dates of NS relapse prior to assignment.No history of treatment with any immunosuppressant for NS.Observation of steroid sensitivity during the treatment of relapse immediately prior to assignment.CD20-positive cell count of at least 5/μL in peripheral blood.Ability to stay in the hospital overnight on all days of planned investigational drug administration.Provision of consent by the patient (aged 20 years or older) or a legal representative (parents or legal guardians) using a document approved by the institutional review board after receiving an adequate explanation regarding the implementation of this clinical trial.

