## Discussion

Herein, the protocol for a multicenter, double-blind, randomized placebo controlled trial to investigate the efficacy and safety of rituximab for the treatment of childhood-onset early-stage uncomplicated FRNS/SDNS is described. This trial has several strengths.

First, it is a multicenter and double-blind protocol. To date, only two major reports have assessed the use of rituximab in early-stage uncomplicated SDNS. Ravani et al. conducted a multicenter, open-label, randomized, control trial [10] and Basu et al. conducted a single-center, parallel-arm, open-label, randomized, clinical trial [11]. Compared with these previous reports, our trial is of high quality as clinical research. As the efficacy and safety of drugs can vary depending on geographic location, to evaluate the efficacy of rituximab, a multicenter trial of a Japanese population is therefore needed.

Second, this study also features an unblinded phase. In this manner, it will be possible to clarify the effects and side effects of rituximab by comparing the efficacy and safety during the placebo treatment phase and the active drug treatment phase. Additionally, this study will increase the treatment options for children who experience treatment failure.

Third, the protocol alleviates concerns about treatment compliance because the medication is administered via intravenous infusion. As current recommended immunosuppressive drugs have serious side effects, and it is necessary to continue oral administration each day or every other day, a lack of treatment compliance is common.

Fourth, several clinical benefits may be observed in the rituximab group at the end of the study period. One potential benefit is good renal function because of the absence of calcineurin inhibitor-associated renal vasoconstriction and chronic nephrotoxicity. Other possible benefits include catch-up growth and weight loss because of corticosteroid sparing.

Finally, this trial has multiple secondary endpoints. Assessing the relationship between recurrence and the number of B cells may help to determine the pathology of NS. However, our study has limitations, including a small sample size and its short-term duration.

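### The Fisher 2x2 table for B-cell normalisation against relapse ignores which event came first, although both event times will be available (minor, exploratory)

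*Protocol article*

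**What the plan says.** The Statistical analysis section relates B-cell normalisation to two outcomes in one sentence, which opens "The relationships of normalization of the number of peripheral blood B-cells with the presence or absence of relapse" and ends "with the presence or absence of relapse and with adverse events will be evaluated in each blinded observation period using Fisher’s exact test". Both sides of the comparison are yes/no, and nothing in the sentence uses dates.

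The dates will exist. The preceding sentence reads "Median of the time to normalization of peripheral blood B-cells and its 95% confidence interval will be estimated using the Kaplan-Meier method". The Outcomes section defines relapse-free survival over days 1–365, "assessed as the period from the date of assignment/allocation until that of the first relapse following the commencement of investigational drug administration".

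The Discussion gives the analysis a mechanistic purpose: "Assessing the relationship between recurrence and the number of B cells may help to determine the pathology of NS".

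The article does not say whether the test uses rituximab-treated patients only or both arms, whether B-cell status is scored to day 365 or only up to relapse, or what count is normal. Those details may stand in the full protocol or analysis plan. Their absence here is not the point. The point is the method that the article does fix.

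**The concern.** The question of interest is whether relapse tends to follow B-cell recovery. A table of ever normalised by ever relapsed counts a relapse before recovery exactly like one after it, so it cannot show order.

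Two opposite errors can follow. If most rituximab patients normalise within the year, the not-normalised row is nearly empty and a real link is missed. If scoring ends at relapse, patients who relapse early have less time in which to normalise, and the table shows an association where none exists, with relapse appearing to go with absence of recovery.

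At stake is a mechanistic statement that the Discussion counts among the trial's strengths. The efficacy conclusion is not at stake.

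**Working it through.** **Inputs from the article.** Sample size section: "relapse-free rates at 1 year of 0.66 in the rituximab group and 0 in the steroid alone group", and for placebo "assuming that the relapse-free rate in 1 year of steroid treatment alone was 0.01 as the placebo group"; 20 patients per group. The planning hazards reproduce: −ln(0.66) = 0.416 and −ln(0.01) = 4.605, against the stated 0.42 and 4.60. Expected relapses by one year are 20 × 0.34 = 6.8, about 7, on rituximab and 20 × 0.99 = 19.8, about 20, on placebo. The article gives no figure for the B-cell analysis itself, so there is none to reproduce.

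**Step 1: order is lost.** Take 16 of 20 normalised, with 7 relapsed and 9 not, and 0 of 4 relapsed among the rest. Fisher gives p = 0.25 whether all seven relapses came before normalisation or after it.

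**Step 2: strongest possible link, rituximab arm only.** All 7 relapses fall among the m patients who normalise by day 365. The probability of that table is C(m,7)/C(20,7), with C(20,7) = 77,520. For m = 14 it is 3,432/77,520 = 0.0443. The two tables in the other tail that are no more probable add 0.0070 and 0.0002, so the two-sided p is 0.0515.

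| Normalised by day 365 | Two-sided p |
|---|---|
| 20/20 | 1.00 |
| 18/20 | 0.52 |
| 16/20 | 0.25 |
| 14/20 | 0.0515 |
| 13/20 | 0.044 |
| 10/20 | 0.003 |

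The article does not state sidedness for this test. The cut falls at the same place one-sided at 2.5%: 0.0443 at m = 14, and 1,716/77,520 = 0.0221 at m = 13.

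**Step 3: power when relapse occurs only after recovery.** Assumptions not in the article: log-normal recovery time with coefficient of variation 0.35, and B cells scored to day 365. The one-year relapse rate is the planning value of 0.34. There were 2,000 simulated trials with 20 rituximab patients.

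| Median recovery (months) | Fisher | Time-dependent Cox score test |
|---|---|---|
| 6 | 0.00 | 0.30 |
| 8 | 0.01 | 0.73 |
| 9 | 0.08 | 0.90 |
| 10 | 0.34 | 0.98 |
| 12 | 0.94 | 1.00 |

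With no true link the time-dependent test rejects in 4–6% of trials.

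**Step 4: a weaker link.** Assumed relapse hazard is 0.15 per year before recovery and ten times that after, with median recovery of 180–300 days and log-SD 0.35. Fisher power is 0.1–6%; the time-dependent test has about 43–56%. The relapse count is not fixed at 7 here. A patient recovering at day 180 has cumulative hazard 0.15 × 180/365 + 1.5 × 185/365 = 0.074 + 0.760 = 0.834, a relapse risk of 57%. At day 300 it is 0.123 + 0.267 = 0.390, or 32%. So the scenario implies roughly 6 to 11 relapses among 20.

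**Step 5: scoring stopped at relapse, no true link.** Fisher in the rituximab arm rejects in 51–72% of trials at median recovery of 180–300 days, and in 26–75% over medians of 5–12 months. The time-dependent test stays at about 4–5%.

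**Step 6: pooling, if it were done, with no link within arms.** All patients enter with "CD20-positive cell count of at least 5/μL in peripheral blood", and placebo does not deplete B cells. If placebo is coded as not normalised and all rituximab patients normalise, the table is 7/20 against 20/20 relapsed, p = 0.000013, which is the treatment-by-relapse table itself. If placebo is coded as normalised, false rejection is 10%, 23%, 36% and 64% at medians of 8, 9, 10 and 12 months, but only about 0–2% at 5–7 months.

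**The case against.** The strongest reply is that the size and even the direction of the error rest on a recovery time and a scoring rule that the article does not give. That stands. A reader might infer that the table cannot detect recovery-driven relapse at all. That is too strong: at about half normalised by day 365, Fisher has about 94% power for a fully recovery-driven relapse, although it still cannot show order.

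A reader might also infer that the test merely restates the treatment effect. The article does not support this either. It never says the arms are pooled, and speaking of normalisation suggests patients who were first depleted. Exact restatement needs one particular coding of placebo together with complete normalisation on rituximab. The phrase about each blinded observation period is unclear for a trial with one such period; if the unblinded phase is also meant, everyone there receives rituximab and pooling of arms does not arise.

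It is also fair to say that the Discussion claims only that the relationship may help, that it concedes a small sample, and that the proposed replacement would miss a tenfold hazard increase about half the time.

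None of this removes the core. Fisher's test on undated outcomes is a stated method, and the dated data are already part of the plan.

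**Conclusion.** The point holds as a minor one. The article fixes a test that ignores time order for a question about time order. With about 7 relapses among 20, it has little power if 14 or more rituximab patients normalise by day 365 and adequate power if about half do. If scoring stops at relapse, it produces a false association in roughly half or more of trials. Which of these applies cannot be settled from the article. The relapse count comes from the planning rate; recovery times, their spread and the tenfold hazard ratio are assumptions. Any contamination by the treatment effect is conditional on pooling and on how placebo is coded. The primary log-rank comparison, the sample size and the efficacy conclusion are unaffected.

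**What to change.** In rituximab-treated patients, analyse time to first relapse with B-cell normalisation as a time-varying covariate in a Cox model. A landmark analysis, or relapse rates per patient-month before and after recovery, would also serve. Use a score test or penalised likelihood, since the hazard ratio has no finite estimate if no relapse precedes recovery. Stratify by phase if unblinded-phase patients are added. Analyse adverse events as rates per person-time before and after recovery. State how placebo patients are handled and label the results exploratory. A 2x2 table may remain as description.

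The cost is a change of wording and a few lines of code, with no new data. There are two drawbacks. The recovery date is known only to within a visit interval, and the width of that interval cannot be judged here because the schedule tables are not shown. Power also stays moderate with so few relapses, so the estimate and its interval should be reported rather than a verdict from a p-value.

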### Coordinating center

The coordinating center will provide various clinical trial coordination activities, including protocol preparation support and project management, to facilitate the activities of the clinical trial coordination committee.

## Discussion

Herein, the protocol for a multicenter, double-blind, randomized placebo controlled trial to investigate the efficacy and safety of rituximab for the treatment of childhood-onset early-stage uncomplicated FRNS/SDNS is described. This trial has several strengths.

First, it is a multicenter and double-blind protocol. To date, only two major reports have assessed the use of rituximab in early-stage uncomplicated SDNS. Ravani et al. conducted a multicenter, open-label, randomized, control trial [10] and Basu et al. conducted a single-center, parallel-arm, open-label, randomized, clinical trial [11]. Compared with these previous reports, our trial is of high quality as clinical research. As the efficacy and safety of drugs can vary depending on geographic location, to evaluate the efficacy of rituximab, a multicenter trial of a Japanese population is therefore needed.

Second, this study also features an unblinded phase. In this manner, it will be possible to clarify the effects and side effects of rituximab by comparing the efficacy and safety during the placebo treatment phase and the active drug treatment phase. Additionally, this study will increase the treatment options for children who experience treatment failure.

Third, the protocol alleviates concerns about treatment compliance because the medication is administered via intravenous infusion. As current recommended immunosuppressive drugs have serious side effects, and it is necessary to continue oral administration each day or every other day, a lack of treatment compliance is common.

Fourth, several clinical benefits may be observed in the rituximab group at the end of the study period. One potential benefit is good renal function because of the absence of calcineurin inhibitor-associated renal vasoconstriction and chronic nephrotoxicity. Other possible benefits include catch-up growth and weight loss because of corticosteroid sparing.

Finally, this trial has multiple secondary endpoints. Assessing the relationship between recurrence and the number of B cells may help to determine the pathology of NS. However, our study has limitations, including a small sample size and its short-term duration.

In conclusion, we are conducting a multicenter, double-blind, randomized placebo controlled trial to evaluate the efficacy and safety of rituximab for early-stage uncomplicated FRNS/SDNS. The results of this study may support the use of rituximab as a first-line corticosteroid-sparing therapy for patients with early-stage uncomplicated FRNS/SDNS.

